### Statistical Methods and Power Calculations

By using StatCal of Epi INFO 2000 software package (Centers for Disease Control and Prevention, Atlanta, GA, USA), a sample size of 21 patients for each group (42 patients for the whole study) has been calculated to reach a confidence level of 95% with a power of 80%, supposing that the hospital stay for LC with H the conversion rate can be reduced from 35% to 3%.

Analysis of data is by intention-to-treat. It will be specified when and how any deviations from randomised allocation, false inclusions, or missing outcomes have been handled. Repeated measures of the outcome will be performed with complete case analyses, potentially excluding individuals with some follow-up data, Eventual missing outcomes will be imputed using baseline values or by assuming that all missing participants have the same risk as the observed participants in the control group.

Data are expressed as numbers (%) and means (SD). The results of the two groups in comparison are analyzed using the Pearson's chi-square test and Fisher exact test, as appropriate, for proportions in case of discrete data. Fisher exact test is used when the data are very unequally distributed among the cells of the table or the expected frequency of any cell is less than 5 or the total N is less than 50. For means in case of continuous numerical data, the independent samples T test and the Mann-Whitney U-test are used, respectively for data normally and non-normally distributed. The data are previously tested for normality by the Kolmogorov-Smirnov test. For multivariate analysis the stepwise logistic regression is applied. A *p*-value of < 0.005 is in any case considered to be statistically significant.

Forward selection has been used as variable selection method; it will include all the baseline variables and all baseline variables are assessed for imbalance. The final model only contain variables with a p-value less than 0.05. Imbalances of baseline variables are defined comparing the groups using t tests for continuous variables and χ^2 ^tests for categorical variables. The adjustments are based upon the stratified logrank test or analysis of covariance. [11-13]The primary outcome is the conversion rate. Secondary outcomes are: intra-operative and post-operative morbidity and mortality, operative time and intra-operative blood losses.

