All the secondary outcomes, including morbidity and mortality, operative time and blood losses, will be controlled as well for imbalances, (i.e. age, previous comorbidities, anticoagulant therapies, previous abdominal surgery).

Inclusion criteria are:

• Adult patients (>18 years)

• Clinical (pain, fever > 37.5°C, WBC > 10.000/microL), and ultrasound evidence of cholecystitis

• ASA I-III patients

• Informed consent

• Less than 72 h from the onset

Exclusion criteria are:

• Informed consent refusal

• Choledocholithiasis

• Generalized peritonitis

• Previous abdominal surgical procedures

• Patients with an intra-operative findings of different pathology will be excluded from the study

• Apache II score > 10

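### The supportive adjusted analysis (forward-selected logistic regression over all baseline variables, about 8 conversions expected) is unsuitable and often gives no finite treatment estimate; the unadjusted Fisher test is unaffected

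*Protocol article*

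**What the plan says.** All of the following is in the protocol article, under Statistical Methods and Power Calculations, unless another section is named.

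- **Size.** "a sample size of 21 patients for each group (42 patients for the whole study) has been calculated", for a fall in conversion from 35% to 3% with 95% confidence and 80% power.
- **Unadjusted comparison.** Proportions are compared by chi-square or Fisher exact test. Fisher applies when the total is below 50, so it applies here.
- **Multivariable model.** "For multivariate analysis the stepwise logistic regression is applied". On how it is built: "Forward selection has been used as variable selection method; it will include all the baseline variables". The final model keeps only variables with p < 0.05.
- **Imbalance.** Baseline differences are judged by t tests and chi-square tests.
- **Adjustment.** "The adjustments are based upon the stratified logrank test or analysis of covariance".
- **Secondary outcomes.** These are also to be controlled for imbalances. The list of examples ends with "anticoagulant therapies, previous abdominal surgery", while the exclusion criteria just below it include "Previous abdominal surgical procedures".
- **Candidate variables.** The Data Collection section lists 15 preoperative items: stone history, four associated diseases, duration of complaints, palpable gallbladder, temperature, six laboratory values and ultrasound findings. The Intervention section adds demographics and further comorbidity classes.

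**The concern.** The article does not leave the adjusted analysis to a later document; it prescribes a method. That method chooses covariates from the trial's own data, from a pool larger than the expected number of events. Three consequences follow.

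1. The chosen covariates would largely reflect chance.
2. With few or no conversions under H, ordinary logistic regression has no finite treatment estimate to report.
3. If treatment is itself subject to the p < 0.05 retention rule, it can be missing from the model that is meant to describe its effect.

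In addition, the log-rank option has no defined time-to-event outcome to act on, and one named adjustment factor cannot vary if the exclusion is applied. At stake is the credibility of a second, adjusted result for conversion that would be reported beside the unadjusted one, with no statement of which prevails.

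**Working it through.** **Inputs.** From the article: n = 21 per group; conversion 35% (MD) and 3% (H); retention at p < 0.05; a 3.9% conversion rate for H from a retrospective series (Background). My assumptions: two-sided alpha 0.05, a 10% H rate as a pessimistic value, and 10 to 20 candidate variables.

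**1. The plan's sample size.**
- Pooled variance, no continuity correction: n = [1.96·√(2·0.19·0.81) + 0.842·√(0.35·0.65 + 0.03·0.97)]² / 0.32² = 22.4, so 23 per group.
- Unpooled variance: (1.96 + 0.842)²·(0.2275 + 0.0291) / 0.32² = 19.7, so 20 per group.

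The stated 21 lies between the two, so the design rates can be taken as the basis for what follows.

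**2. Expected events.** 21 × 0.35 + 21 × 0.03 = 7.35 + 0.63 = 7.98. The exact binomial probability of 5 to 11 events is 0.932 − 0.061 = 0.87. Events per candidate: 7.98/10 = 0.80, 7.98/15 = 0.53, 7.98/20 = 0.40.

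**3. No conversion in the H group.**

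| True H rate | P(0 of 21) |
|---|---|
| 3% (design) | 0.97^21 = 0.53 |
| 3.9% (Background) | 0.961^21 = 0.43 |
| 10% (assumed) | 0.90^21 = 0.11 |

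With an empty cell the maximum-likelihood odds ratio is 0, and its log and Wald standard error are not finite, before any covariate is added.

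**4. A worked table.** Take 0/21 against 7/21, the nearest whole numbers to the design with no H event.
- Fisher, two-sided: 2 × C(21,7)/C(42,7) = 2 × 116,280/26,978,328 = 0.0086.
- Likelihood ratio: log-likelihood with treatment 7·ln(1/3) + 14·ln(2/3) = −13.37; without, 7·ln(1/6) + 35·ln(5/6) = −18.92; statistic 2 × 5.557 = 11.11, p = 0.0009.
- Wald: no finite estimate or interval.

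A test of treatment can still be obtained, but the answer depends heavily on which test is used.

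**5. Chance selection.** For k independent irrelevant covariates, each screened once at 0.05, P(at least one passes) = 1 − 0.95^k: 0.40 (k = 10), 0.54 (k = 15), 0.64 (k = 20). Forward selection was then simulated at the design rates: 42 patients, independent non-prognostic covariates, half binary (15–40% prevalence) and half normal, likelihood-ratio entry at p < 0.05, 400 trials per setting, Monte Carlo error about 2.5 points.

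| Result | 10 candidates | 20 candidates |
|---|---|---|
| At least one irrelevant variable entered | 48% | 77% |
| Final model without finite estimate | 65% | 77% |
| Same, treatment forced in | 60% | 70% |
| Treatment absent (if not forced) | 15% | 16% |

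A second simulation of the rule at the design rates gave 52–75% for chance entry, 61–70% for a separated final model and about 15% for absent treatment.

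**6. Type I error for treatment.** A null simulation used 42 patients, event rate 19% or 35%, 10 or 20 irrelevant covariates, and selection capped at five with treatment added afterwards (600 trials per setting, Monte Carlo error about 1 point). It gave 2.7–5.8% (Wald) and 5.5–7.5% (likelihood ratio), against 4.7–6.8% for the unadjusted likelihood-ratio test. Any inflation is small and depends on the test.

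**7. Text against text.** Conversion is a yes/no event during surgery. The article defines no time-to-event outcome, so the log-rank option has nothing stated to apply to. Previous abdominal surgery is both an exclusion and an adjustment example; among eligible patients it is constant.

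**The case against.** The strongest reply is that the primary comparison does not depend on any of this. With 42 patients the plan's own rule calls for Fisher's exact test, and no sentence makes the regression co-primary. That stands and limits the point to a supportive analysis.

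A reader might infer several stronger things that the article does not support:

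- *That no valid adjusted result is possible, or that no p-value exists.* Under separation a likelihood-ratio or score test usually survives, as step 4 shows. What is lost is the finite estimate and Wald interval.
- *That the treatment p-value is anti-conservative.* Entry of irrelevant covariates is not the same as false-positive treatment effects in a randomised comparison, and step 6 shows no material inflation. It covers only non-prognostic covariates, with treatment added after selection. P-values of the selected covariates do suffer from selection.
- *That half of all trials would have no H conversion.* This holds only if the optimistic 3% is true.
- *That log-rank is prescribed for conversion.* It is offered as an alternative to analysis of covariance and assigned to no outcome. Covariance analysis suits operative time and blood loss. Undefined strata are the kind of detail an article leaves out.
- *That treatment will be dropped.* The selection sentence speaks of baseline variables; whether treatment is forced in is unstated. This is an ambiguity.
- *That the previous-surgery entry biases results.* A constant covariate simply drops out, and the list is attached to secondary outcomes.

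One further counterpoint fails: that all baseline variables form a candidate pool and not one saturated model. This is true, but the simulated procedure already treats them as a pool.

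**Conclusion.** The point holds in limited form. The adjusted analysis that the article fixes does not suit a trial expecting about 8 conversions. At the design rates the treatment odds ratio has no finite maximum-likelihood value in 53% of trials from the H group alone (43% at 3.9%, 11% at 10%). After forward selection the final model lacks a finite estimate in roughly 60–77%. Irrelevant variables enter in roughly half to three quarters of trials. These simulated figures rest on the design rates, on 10 to 20 candidates and on independent, non-prognostic covariates; the 15–16% for absent treatment also assumes that treatment competes for entry.

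The log-rank option lacks a defined outcome, and the previous-surgery passages contradict each other. The unadjusted Fisher test of conversion stands, and inflated type I error for treatment is not established. This should be corrected, but it does not undermine the primary comparison.

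**What to change.** - State that the unadjusted Fisher exact test, reported with the risk difference and an exact 95% confidence interval, is decisive for conversion, and that any adjusted model is supportive only. Fisher is already the plan's test; its precedence is what needs saying.
- Delete the baseline significance tests, forward selection and the log-rank option.
- For conversion and the other sparse binary outcomes (morbidity, mortality), use Firth-penalised or exact logistic regression with treatment forced in and at most one or two covariates. These should be already collected and named before the data are seen, on clinical grounds that the investigators state.
- For operative time and blood loss, use analysis of covariance with the same covariates and a measurement scale fixed in advance.
- Take previous abdominal surgery off the adjustment list, or otherwise reconcile it with the exclusion criterion.

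**Cost.** Changes of analysis wording only, with no new patients or data. Data-driven exploration is given up. Software other than the named Epi Info 2000 may be needed for the penalised model; this should be checked.

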### Data Collection

Patients' data sheets are generated containing demographic data and preoperative, operative, and postoperative information.

Pre-operative notes concern the history of gallbladder stones, the presence of associated diseases (cardiac, hypertension, diabetes, malignancy), duration of gallbladder complaints (as an indication for the onset of the disease), finding of a palpable gallbladder, temperature, and laboratory results of WBC count, serum bilirubin, gamma GT, CRP, IL-6 and alkaline phosphatase.

Ultrasound findings are also reported.

Operative data of concern are macroscopic findings (of acute cholecystitis, gangrenous cholecystitis, hydrops, and empyema of the gallbladder), the presence of small stones (< 1 cm diameter) or large bile stones (> 1 cm diameter), information regarding perforation of the gallbladder and intraperitoneally "lost" stones, reasons for conversion, and duration of surgery. Postoperative notes of interest included the use of nasogastric tubes and drains, the amount of analgesics used, (evaluation of pain with VAS score), complications, and length of hospital stay.

Complications are classified as surgical infections (wound infection, subphrenic or subhepatic abscess); noninfectious surgical problems (e.g., bile duct injury, hemorrhage); remote infections (urinary or respiratory); and miscellaneous problems (e.g., atelectasis, deep vein thrombosis, AMI, CVA, etc). The collected information are entered into a database as either continuous or categorical variables for statistical analysis. Following the operative procedure, a normal sterile dressing will be applied to cover the abdomen.

A second surgical team, aware of the operative findings but not the surgical dissection instrument, then will assume the care of the patient. Postoperative care and ability to be discharged from the hospital will be determined by the second surgical team. The primary operative team will be in every moment available for emergent consultation.

Patient discharge will be base on good medical practice criteria: 1) apyrexia 2) absence of diseases requiring hospitalisation 3) return of bowel function 4) patient's compliance.

No Placebo drugs are used for this study.

Every patient will be asked to sign the Informed Consent.

In the informed consent form, patients will receive all the information about the study protocol, the confidential nature of personal data and will fill up a questionnaire before signing or refuse.

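### Adjustment of operative time and blood loss for preoperative severity is not secured: the named covariates omit it and conflict with the rule covering all baseline variables

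*Protocol article*

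**What the plan says.** Two statements in Statistical Methods and Power Calculations govern covariates.

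- **General rule.** "For multivariate analysis the stepwise logistic regression is applied". Forward selection follows, of which the article says "it will include all the baseline variables and all baseline variables are assessed for imbalance" and "The final model only contain variables with a p-value less than 0.05". Imbalance is judged by t tests and chi-square tests between arms, and adjustment is to be by a stratified log-rank test or analysis of covariance.
- **Rule for the secondary outcomes.** After naming them (morbidity, mortality, operative time, blood loss), the section says that they "will be controlled as well for imbalances, (i.e. age, previous comorbidities, anticoagulant therapies, previous abdominal surgery".

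The exclusion criteria that follow the second statement rule out patients with earlier abdominal operations.

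Data Collection lists the preoperative record. It includes "duration of gallbladder complaints (as an indication for the onset of the disease" and "finding of a palpable gallbladder, temperature, and laboratory results of WBC count, serum bilirubin, gamma GT, CRP, IL-6 and alkaline phosphatase", and adds: "Ultrasound findings are also reported".

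**The concern.** The four named covariates describe the patient's background. None describes the acute inflammation that the surgeon has to dissect, although several candidate markers are already recorded. If severity predicts operative time and blood loss, leaving it out has two costs. The standard errors are larger than they need be, and a chance difference in severity between two arms of 21 stays inside the treatment estimate.

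The list also has faults of its own. One of its four entries cannot vary among eligible patients, and it does not match the rule that puts all baseline variables in play.

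**Working it through.** **Arm size.** The article plans 21 per group for conversion rates of 35% and 3%, with 95% confidence and 80% power. The two-sided pooled formula gives

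n = [1.960·√(2·0.19·0.81) + 0.842·√(0.35·0.65 + 0.03·0.97)]² / 0.32² ≈ 22.4, so 23 per group.

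The unpooled formula gives 19.7, so 20. The planned 21 lies between the two and is used below. The article gives no planning figure for operative time or blood loss.

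**What each reading of the covariate text delivers**

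| Reading of the secondary-outcome list | Severity in the analysis of operative time and blood loss? |
|---|---|
| Closed list, as *i.e.* suggests | No. Three usable covariates remain, none of severity. |
| Illustrative, with the general rule extended to secondary outcomes | Only if a marker is flagged by a baseline test or kept by forward selection. That selection is described after a logistic model, whereas these two outcomes are continuous. |

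Neither reading guarantees a severity covariate.

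**How far the imbalance test reaches.** For a standardised covariate, the difference between arms has SD √(2/21) = 0.309 (normal approximation).

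- P(difference > 0.3 SD) = 0.33; P(difference > 0.5 SD) = 0.105.
- A test at 0.05 flags a difference above 1.960 × 0.309 ≈ 0.60 SD. At 0.005, the article's general significance level, the limit is about 0.87 SD. The article does not say which level applies to baseline tests.
- Under sound randomisation a test at 0.05 flags any given marker in 5% of trials. So in about 10.5% − 5% = 5.5% of trials the marker differs by more than 0.5 SD and is not flagged.
- An unflagged 0.5 SD difference moves the outcome comparison by 0.5 × r, where r is the within-arm correlation of marker and outcome. For assumed r of 0.3, 0.5 and 0.7 the shift is 0.15, 0.25 and 0.35 SD.

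**Precision at stake.** The article gives neither an SD nor a correlation, so the share of variance explained (R²) is assumed. For two covariates and 42 patients, the variance ratio is approximately (1 − R²) × 40/38.

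| Assumed R² | Variance ratio | SE ratio | Equivalent gain in patients |
|---|---|---|---|
| 0.10 | 0.947 | 0.973 | 6% |
| 0.20 | 0.842 | 0.918 | 19% |
| 0.30 | 0.737 | 0.858 | 36% |

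Break-even is at 1 − R² = 38/40, that is R² = 5%. With one covariate it is 1 − 39/40 = 2.5%.

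**The same in detectable differences.** For one covariate, two-sided 0.05, 80% power and ignoring the lost degree of freedom, the detectable difference is 2.802 × 0.309 × √(1 − r²). That is 0.865 SD unadjusted, and 0.825, 0.749 and 0.617 SD for r of 0.3, 0.5 and 0.7.

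**The case against.** A reader might infer that severity imbalance is left uncorrected. The article does not support that. Its general rule takes in all baseline variables, and the preoperative markers are among them. Analysis of covariance is a method for continuous outcomes, so the adjustment route is not confined to the logistic model. The wording for the secondary outcomes appears to extend that scheme to them. A list containing an excluded condition is also hard to take as a considered, exhaustive set. This much stands: severity is not barred.

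A reader might also infer a biased treatment effect. Randomisation keeps the unadjusted comparison unbiased on average, and a difference of 0.3 SD at this sample size is ordinary chance.

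The size of the gain is open too. The article does not say that these markers predict operative time or blood loss. Eligibility truncates three of them (onset within 72 hours, a temperature threshold and a white cell threshold), which points to the lower end of the range for those three. CRP has no eligibility cut-off.

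Finally, a covariate set for secondary outcomes is often left to the analysis plan. Here, though, the article does name a set, and that set conflicts with its own general rule and exclusion criteria. That needs correcting wherever the detail ends up.

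The objection does not rescue the route itself. A baseline test asks whether the arms differ, but the gain in precision comes from how well the covariate predicts the outcome. A strongly predictive marker that happens to be balanced would fail the imbalance test, and its gain would be lost.

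**Conclusion.** The point holds as a failure to secure severity adjustment; the article does not rule it out. The named list has no severity marker, includes an item that is constant among eligible patients, and disagrees with the rule on all baseline variables. The fallback of testing for imbalance misses differences below about 0.6 SD with 21 per arm.

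The consequence is lost precision and exposure to chance imbalance in two secondary outcomes. It is not systematic bias, and it does not touch the conversion-rate comparison. Under an assumed R² of 10% to 30% from two covariates, the loss is about 3% to 14% in standard error. That range rests wholly on the assumption that preoperative severity predicts these outcomes; the lower end is modest.

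**What to change.** 1. Reconcile the two statements, so that one covariate set applies to operative time and blood loss.
2. Drop previous abdominal surgery from the list, since the exclusion criteria as written make it constant.
3. Prespecify, for example: *Operative time and blood loss will each be analysed by analysis of covariance, on a suitable scale fixed in advance, on arm plus a short fixed covariate set that includes log CRP recorded before randomisation, with or without symptom duration. The model will be fitted whether or not the arms look imbalanced, and the unadjusted comparison will be reported alongside.*
4. Do not use the macroscopic operative findings as covariates, because they are recorded after randomisation.

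The cost is wording only: the markers are already in the planned preoperative record, and the article already names analysis of covariance. Each severity covariate takes one degree of freedom. Intervals would widen slightly if two covariates explained less than about 5% of the variance.

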## Methods

The study project is a prospective, randomized investigation. The study will be performed in the Department of Emergency Surgery St Orsola-Malpighi University Hospital (Bologna, Italy), a large teaching institutions, with the participation of all surgeons who accept to be involved in.

The Ethic Committee of St. Orsola Malpighi University Hospital has approved the study protocol on June 24^th ^2008. The study and its Informed Consent form have been judged by the Committee to be ethically and scientifically satisfactory as well as correct and adequate to the aims.

The patients will be allocated in two groups: in the first group the patient will be submitted to early LC within 72 hours after the diagnosis with H while in the second group will be submitted to early LC within 72 hours with MD.

The randomization will be obtained through computer-generated schedule. Blocked randomization is used to ensure close balance of the numbers in each group at any time during the study. The result of this randomization will be sealed in numbered envelopes, inserting inside a cardboard to ensure that they are opaque. After cholecystitis diagnosis if the patient fulfils the inclusion criteria the responsible surgeon will ask the patient to partecipate to the study. If the patient agree, he/she will sign the informed consent. After patient's consent the randomization will be carried out. The responsible surgeon will record the patient name (and number). [7-9]

All eligible patients will be recorded. [10]

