### Intervention

Preoperative data collected will include patient demographics and comorbidity conditions (genitourinary, cardiac, pulmonary, gastrointestinal, renal, or rheumatologic) and a detailed history of symptom onset.

The procedure was performed by a surgeon that had performed at least 50 LCs.

On admission, the patients were started on cefotaxime, 2 g IV every 12 h, which was continued postoperatively according to NNISS score.

The standard four-trocar operative technique is used for LC for acute cholecystitis.

When the gallbladder is distended it will be first aspirated. To allow a good hold on the gallbladder larger graspers will be inserted through a 5 mm right lower port. The cystic artery and duct are clip-ligated in the MD group whereas in the H group cystic artery and duct are closed by H. In the H group the surgeon will use only H, whereas in the MD group the surgeon will use only MD. The gallbladder and intraperitoneal "dropped" stones are collected in an endoscopic bag and extracted through the umbilical cannula site, which can be extended. A closed system suction drain is left. Fascial closure is attempted only at the umbilical cannula site. The skin at all the cannula sites are closed with staples. Conversion to laparotomy will be decided by the operating surgeon and each conversion will be motivated.

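### Excluding randomised patients for a different pathology found at operation contradicts the stated intention-to-treat analysis and can bias the conversion comparison

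*Protocol article*

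**What the plan says.** Four statements in the protocol article bear on this point.

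- **Order of events (Methods).** A patient is diagnosed, checked against the inclusion criteria and asked for consent. Then: "After patient's consent the randomization will be carried out". The allocation is held in numbered opaque envelopes. Opening them is not tied to any step in the operation.
- **Exclusion (last subsection before Intervention, list of exclusion criteria).** "Patients with an intra-operative findings of different pathology will be excluded from the study".
- **Analysis population (Statistical Methods and Power Calculations).** "Analysis of data is by intention-to-treat". The next sentence reads: "It will be specified when and how any deviations from randomised allocation, false inclusions, or missing outcomes have been handled".
- **Who knows the arm and who decides the outcome (Intervention; Data Collection).** "In the H group the surgeon will use only H, whereas in the MD group the surgeon will use only MD". "Conversion to laparotomy will be decided by the operating surgeon and each conversion will be motivated". Blinding is described only for those who take over after surgery: "A second surgical team, aware of the operative findings but not the surgical dissection instrument, then will assume the care of the patient".

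The primary outcome is the conversion rate. The article describes no replacement of excluded patients.

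**The concern.** Intention-to-treat means that everyone randomised is analysed in the arm assigned. An exclusion triggered by something seen during the operation removes people after that point. The two rules give different analysis sets, and the article does not say which one prevails.

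Some post-randomisation exclusions are tolerable: those that rest on facts fixed before allocation and are judged by someone who knows neither the arm nor the outcome. The pathology itself does precede allocation. Its recognition and labelling do not, and no blinded judgement is described. What counts as a different pathology is also undefined. If being labelled is related to arm, or to whether the operation was converted, the comparison of conversion rates is no longer protected by randomisation. With few expected events, one or two such removals matter.

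**Working it through.** **Inputs from the article.** 21 patients per group; conversion 35% with MD and 3% with H; 95% confidence and 80% power for sizing; results called significant at p < 0.005; Fisher's exact test when the total is below 50. Two-sided testing is assumed, since sidedness is not stated.

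**The plan's own figure.** For a two-sided 0.05 test with 80% power:

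- pooled variance: n = [1.96·√(2·0.19·0.81) + 0.8416·√(0.35·0.65 + 0.03·0.97)]² / 0.32² = 22.4, so 23 per group;
- unpooled variance: n = (1.96 + 0.8416)²·(0.2275 + 0.0291) / 0.32² = 19.7, so 20 per group.

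The stated 21 lies between them, so the inputs are read correctly.

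**Expected events.** 21 × 0.35 + 21 × 0.03 = 7.35 + 0.63 = 7.98.

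**Effect of removing one converted H patient (two-sided Fisher p, MD vs H).** Both thresholds are shown because the article sizes at 0.05 and declares significance at 0.005.

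| All randomised | p | One H conversion removed | p | Threshold crossed |
|---|---|---|---|---|
| 8/21 vs 1/21 | 0.020 | 8/21 vs 0/20 | 0.0034 | 0.005 |
| 9/21 vs 1/21 | 0.0089 | 9/21 vs 0/20 | 0.0013 | 0.005 |
| 6/21 vs 1/21 | 0.093 | 6/21 vs 0/20 | 0.021 | 0.05 |
| 7/21 vs 2/21 | 0.130 | 7/21 vs 1/20 | 0.045 | 0.05 |
| 8/21 vs 2/21 | 0.067 | 8/21 vs 1/20 | 0.020 | 0.05 |
| 7/21 vs 1/21 | 0.045 | 7/21 vs 0/20 | 0.0086 | none |
| 6/21 vs 2/21 | 0.238 | 6/21 vs 1/20 | 0.093 | none |

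The last two rows have exactly 8 events. There, one removal crosses neither threshold. Two can: 6/21 vs 2/21 (p=0.238) becomes 6/21 vs 0/19 (p=0.021).

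**How often one removal would change the result.** Let a be MD conversions, binomial (21, 0.35), and b be H conversions, binomial (21, 0.03). Sum P(a)·P(b) over all tables with b ≥ 1 that are non-significant in full and significant in favour of H once one H conversion is removed.

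- At 0.005: 8–1 (0.0580) + 9–1 (0.0451) + 10–2 (0.0090) + 11–2 (0.0049) + rarer splits (0.0004) = about 0.12.
- At 0.05: 6–1 (0.0534) + 5–1 (0.0372) + 7–2 (0.0190) + 8–2 (0.0180) + rarer splits (0.0029) = about 0.13.

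H has no conversion to remove with probability 0.97²¹ = 0.53.

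**The reverse direction.** Under the same enumeration, removing one MD conversion never turns a significant full table non-significant at either threshold. Removing two can: 7/21 vs 1/21 (p=0.045) becomes 5/19 vs 1/21 (p=0.085).

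**No true difference (assumed 20% in both arms, 0.05).** False wins for H rise from 1.2% to 4.1% if one H conversion is dropped whenever one occurs, and to 9.9% if up to two are dropped.

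**Loss of numbers alone (assumed 1, 2 or 3 per arm, unrelated to outcome).** Exact Fisher power falls from 73% to 70%, 67% and 63% at 0.05, and from 30% to 26%, 22% and 18% at 0.005.

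**The case against.** The strongest defence has four parts.

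1. **The article anticipates false inclusions.** It says their handling will be specified, and it collects macroscopic findings and reasons for conversion. This stands as evidence of awareness and gives the data needed for a sensitivity analysis. It does not put the patients back: the exclusion bullet has already fixed that they leave.
2. **The pathology was there before allocation.** If it is recognised and labelled equally in both arms, and independently of conversion, dropping these patients costs precision and does not bias the comparison. That is correct. It is why the claim is that the rule *can* bias the comparison.
3. **Such cases may be rare.** Entry requires clinical and ultrasound evidence of cholecystitis. No frequency is given, so this can be neither confirmed nor refuted.
4. **The scenarios are selected.** They assume that the removed patient is a converted H patient, and more than half of trials run under the design rates would have none. This also stands, so the probabilities above are conditional on that assumption.

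A reader might go further and infer three things that the documents do not support. One is that the unblinded operator decides the exclusion: the article names no decision-maker. Another is that unexpected pathology leads to conversion, so that events are selectively removed: this is plausible, but the article says only that each conversion will be justified. The third is that a single exclusion overturns a result at the expected 8 events: at exactly 8, one removal crosses neither threshold.

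**Conclusion.** The contradiction holds as written: randomisation before surgery, removal on an operative finding, and an intention-to-treat claim cannot all be followed. It needs correcting whatever its numerical effect, because applying the exclusion rule drops randomised patients from an operation whose surgeon knows the instrument and decides the primary outcome.

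The direction and size of any bias are unknown. They depend on how often a different pathology is found and on how its labelling relates to arm and conversion, and the article gives neither. The chance of about 0.12 (at 0.005) or 0.13 (at 0.05) that one removal creates a significant result rests on the design rates, two-sided Fisher tests, and one H conversion being dropped whenever one occurs. It shows how fragile the comparison is to such removals and does not predict what would happen in this trial.

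**What to change.** Delete the bullet as a ground for removing patients. State that every randomised patient enters the primary analysis in the assigned arm. Record the operative diagnosis for all. Report the exclusion of patients with a different pathology only as a sensitivity analysis, with counts and reasons by arm, and preferably classified by someone blind to arm and to conversion.

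The cost is a wording amendment and one data item, which partly exists already in the operative findings. The downside is small: a few patients without acute cholecystitis stay in the primary analysis and may slightly dilute the effect.

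As an optional addition, the envelope could be opened after laparoscopic inspection and before dissection, with both instruments ready in theatre. This would reduce the number of such cases. It does not replace the main change, because a different pathology may become apparent only during dissection.
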